### 2.2 Description of CDMP participants

We will describe baseline characteristics of CDMP participants overall and broken down by year of enrolment (2011, 2012 and 2013). Baseline characteristics will include:

- Age
- Gender
- Aboriginality
- ARIA
- SEIFA

- Source of referral
- Target condition(s)
- Risk of hospitalisation
- Special population flag
- Initial SF1
- Initial intervention
- Reasons for non-enrolment
- Referral target
- Program consent
- Data use consent
- Number of hospitalisations in 2010, average length of hospital stay, total hospital bed days
- Number of unplanned hospitalisations in 2010, average length of unplanned hospital stay, total unplanned hospital bed days
- Number of avoidable hospitalisations in 2010, average length of avoidable hospital stay, total avoidable hospital bed days
- Number of ED admissions in 2010 overall and by triage categories 1-5

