  - "Pelvic inflammatory disease" (where principal diagnosis has ICD-10-AM code as any of N70, N73, N74)
  - "Cellulitis" (where principal diagnosis has ICD-10-AM code as any of L03, L04, L08.0, L08.8, L08.9, L88, L98.0, L98.3)
  - "Gangrene" (where any of the diagnosis fields have ICD-10-AM code as R02)

Secondary efficacy outcomes will include:

1. Unplanned hospitalisations defined as hospitalisations that have status of "emergency" or the mode of separation is not "Transfer to Palliative Care Unit / Hospice" or any of the secondary diagnoses are not "Palliative care "(Z51.5)".
2. Hospital re-admissions defined as admissions occurring less than 30 days after discharge
3. Emergency department admissions
4. Deaths
5. Number of hospital bed-days

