### 3.2.4 *Adjusted analyses*

Both the before-after and the time-dependent analyses will be performed without and with adjustment. Potential covariates will include LHD, age, gender, aboriginality, ARIA, SEIFA, target conditions, SF1 and previous patterns of service utilisation (number of hospitalisations in 2010, number of unplanned hospitalisations in 2010, number of avoidable hospitalisations in 2010 and number of ED admissions in 2010).

Each potential covariate will first be analysed using a univariate Poisson regression and only those with a univariate p-value smaller than 0.20 will be included in the final model. To avoid problems due to colinearity, in case of two covariates with a Pearson correlation coefficient greater than 0.8, only the one with the smallest univariate p-value will be kept in the final model. For covariates with more than 10% of data missing, we will create a separate category labeled “missing”.

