#### *Propensity scoring and matching*

Using baseline characteristics, we will calculate a propensity score defined as the probability of getting enrolled in the program. Matched controls will be selected from the APDC dataset using individuals who never got enrolled into the program. We will follow the following steps:

- Step 1:** Group program participants by period (e.g. month/quarter/semester) according to their enrolment date (the final “grouping period” will depend on the number of participants recruited).
- Step 2:** For each stratum/period, obtain details of the latest hospitalisation occurring in the 12 months preceding the period. Any program participant with no hospitalisation in the preceding 12 months will be excluded from propensity-based analyses.
- Step 3:** Within each stratum/period, calculate propensity score using a logistic regression modeling the probability of getting enrolled in the program. Covariates will include all variables considered for adjusted analyses.
- Step 4:** Within each stratum/period, starting with the earliest period, match 2 non-CDMP participants for each CDMP participant on the propensity score using optimal matching procedures. A control which has been used as a match in an earlier period is no longer available as match for a future period.
- Step 6:** Check the quality of the matching by plotting the propensity score distribution between the cases and controls overall and by period and by calculating the standardised difference for every covariate included in the propensity score calculation.

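### The propensity score contains no measure of baseline bed-days or length of stay, so a matched comparison of bed-days, a secondary outcome, is balanced only indirectly and Step 6 cannot show a residual difference

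*SAP*

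**What the plan says.** - **Outcome.** Section 3.1 lists "Number of hospital bed-days" as the fifth secondary efficacy outcome.
- **Baseline description.** Section 2.2 lists "Number of hospitalisations in 2010, average length of hospital stay, total hospital bed days", and repeats the same three measures for unplanned and for avoidable stays. The list describes program participants only: "We will describe baseline characteristics of CDMP participants overall and broken down by year of enrolment".
- **Covariates.** Section 3.2.4 states: "Potential covariates will include LHD, age, gender, aboriginality, ARIA, SEIFA, target conditions, SF1 and previous patterns of service utilisation". A bracket then spells out the utilisation items: "number of hospitalisations in 2010, number of unplanned hospitalisations in 2010, number of avoidable hospitalisations in 2010 and number of ED admissions in 2010". Neither length of stay nor bed-days is among them.
- **Propensity score.** In section 3.3.1, Step 3 builds the score from the variables considered for the adjusted analyses, so it inherits the 3.2.4 list.
- **Balance check.** Step 6 assesses the matching by plotting the score and by "calculating the standardised difference for every covariate included in the propensity score calculation".
- **Role.** Section 3.3.1 makes the matched comparison the primary analysis of program effect. It describes the outcome as an event rate after the matching period, with avoidable hospitalisations as the example. It does not name bed-days.

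**The concern.** Bed-days are the product of how often people are admitted and how long they stay. The score addresses the first factor with three hospitalisation counts and has no direct measure of the second. If enrolment depends on severity that shows as longer stays at a given number of admissions, participants and matched controls will differ in days per stay before the program starts. Whatever part of that difference persists will appear in the follow-up bed-days ratio and could be read as a program effect, or could hide one.

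The diagnostic has the same gap. Step 6 is limited to covariates in the score, so the matching could look good on every reported standardised difference while baseline bed-days differ. Hospital and ED admissions each have a baseline count in the list. Bed-days has no counterpart, although section 2.2 already plans to derive one for participants.

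**Working it through.** **1. The lists side by side**

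| 2010 measure | Described in 2.2 | In 3.2.4, hence in Step 3 | Checked in Step 6 |
|---|---|---|---|
| Hospitalisations: all, unplanned, avoidable (counts) | yes | yes | yes |
| ED admissions (count) | yes | yes | yes |
| Average length of stay: all, unplanned, avoidable | yes | no | no |
| Total bed-days: all, unplanned, avoidable | yes | no | no |

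Step 2 retrieves details of each person's most recent stay, but nothing makes its length a covariate.

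**2. What counts alone can balance**

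Bed-day rate = admission rate × mean days per stay. If matching equalises admission rates and the program has no effect, then

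bed-day ratio = 1 + (relative difference in days per stay) × (share that persists).

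The SAP gives neither input. For assumed differences of 0% to 20%, with half to all persisting:

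- no difference: 1 + 0 = 1.00
- 10% longer, half persisting: 1 + 0.10 × 0.5 = 1.05
- 20% longer, all persisting: 1 + 0.20 × 1.0 = 1.20

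Shorter stays among participants would move the ratio below 1 in the same way.

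**3. Illustrative simulation (all inputs assumed)**

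- 400,000 people. Log-frailty (SD 0.7) drives the number of stays; an independent log-severity (SD 0.5) drives days per stay.
- Enrolment log-odds = −4 + 0.6 × frailty + g × severity.
- Analysis is restricted to people with at least one prior stay, giving 6,047 to 6,784 enrolled.
- The program has no effect, and each person's expected days per stay carries over fully to follow-up.
- Controls were resampled by the propensity odds, as a stand-in for 2:1 matching. The score used prior admission counts alone, then counts plus log(1 + bed-days).

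There was one run for each g. Ratios are enrolled to controls; each cell shows counts alone → counts plus bed-days.

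| g | Baseline bed-day ratio | Standardised difference, log bed-days | Follow-up bed-day ratio |
|---|---|---|---|
| 0 | 1.00 → 0.99 | 0.01 → 0.00 | 1.14 → 1.13 |
| 0.3 | 1.06 → 1.02 | 0.05 → 0.00 | 1.20 → 1.17 |
| 0.6 | 1.20 → 1.04 | 0.15 → 0.00 | 1.37 → 1.30 |
| 1.0 | 1.28 → 1.06 | 0.21 → 0.01 | 1.50 → 1.38 |

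Before any balancing, the baseline ratio at g = 1.0 was 1.54, so counts alone do remove part of the imbalance (1.54 to 1.28).

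The follow-up ratio exceeds 1 even at g = 0, because one period's count measures frailty imperfectly. That part is not due to the omission. Dividing each follow-up ratio by its g = 0 value isolates the part linked to days per stay:

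- counts alone: 1.196/1.136 = 1.05, 1.368/1.136 = 1.20, 1.499/1.136 = 1.32
- with bed-days: 1.169/1.132 = 1.03, 1.295/1.132 = 1.14, 1.383/1.132 = 1.22

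Adding bed-days closes most of the baseline gap and only part of the follow-up gap.

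**4. Where the variable can safely go**

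The before-after analysis in section 3.2.2 counts events from 1 July 2010. For someone enrolled on 1 January 2011, the before period is July to December 2010: 184 days, all inside the calendar year used for the baseline values. Adding 2010 bed-days to 3.2.4 would put part of the before-period outcome on the covariate side of that model. The matched analysis counts outcomes only after the matching period, and enrolment starts in January 2011, so the overlap does not arise there.

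**The case against.** **The groups are already partly balanced.** This stands. The score includes three hospitalisation counts, ED admissions, age and target conditions, all of which may carry information on bed-days. A reader might infer that the groups are not balanced on bed-days at all. That goes too far: only days per stay lacks a direct measure, and other covariates may absorb some of it. The simulation used admission counts only and may therefore overstate the gap.

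**The stakes are limited.** This also stands. Bed-days is one secondary outcome, and the primary outcome has its own 2010 count in the score. A matched bed-days analysis follows from the outcome list but is not stated.

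**The size is assumed.** Correct. Nothing in the SAP shows that participants' stays are longer, and the range includes no imbalance. For someone enrolled in January 2013, the 2010 values are already two years old, which weakens both the possible bias and the benefit of the fix.

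**Stronger readings that the SAP does not support:**

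- *That leaving out "Risk of hospitalisation" is an error.* Section 2.2 lists it for participants only and does not say how or when it is assigned. Controls drawn from APDC probably have no value, so it could not enter the score. If it is assigned at enrolment, it may reflect the before-period outcome. No bias from its absence is shown.
- *That ED admissions by triage category belong in the score.* No outcome in 3.1 is split by triage.
- *That precision would improve by the squared correlation.* That result belongs to linear adjustment of the outcome. The matched model is a Poisson GEE with no stated covariate adjustment.

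**Conclusion.** The point holds as a narrow, low-cost improvement. The SAP names bed-days as an outcome and lists its baseline value for participants, yet it neither matches on that value nor checks its balance in the comparison it calls primary. The lists alone establish this.

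The consequence is conditional. A matched bed-days comparison could carry a residual difference in days per stay if enrolment depends on length of stay beyond what the counts and other covariates capture. Under the assumed models, the baseline imbalance left after balancing on counts ran from none to 28%. The documents do not show where in that range, or whether in it at all, this program lies. The text does not support a claim that the bed-days result is biased by a given amount, or that the primary outcome is affected.

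**What to change.** Amend Step 3 in section 3.3.1 so that the propensity score uses the variables from 3.2.4 and, in addition, baseline total bed-days and baseline unplanned bed-days, for example each as log(1 + days). Derive them from APDC in the same way for participants and controls, over the same baseline year as the admission counts. Step 6 then reports their standardised differences without further change.

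Leave the 3.2.4 list as it is on this point, because of the overlap with the before period. The four existing 2010 counts already share that overlap, and bed-days should not add to it.

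The cost is one sentence in the SAP and slight extra derivation work for controls. APDC is described in section 1.2 as covering all NSW admissions from January 2007, so the 2010 values should be available for both groups. The change reduces the possible bias without removing all of it, so the bed-days result should still be read with that in mind.

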## 3.3 *Analyses using a control group*

### 3.3.1 *Matched analyses*

The primary analysis for assessing the effect of the program will be performed using a propensity-matched cohort as the comparator.

#### *Propensity scoring and matching*

Using baseline characteristics, we will calculate a propensity score defined as the probability of getting enrolled in the program. Matched controls will be selected from the APDC dataset using individuals who never got enrolled into the program. We will follow the following steps:

- Step 1:** Group program participants by period (e.g. month/quarter/semester) according to their enrolment date (the final “grouping period” will depend on the number of participants recruited).
- Step 2:** For each stratum/period, obtain details of the latest hospitalisation occurring in the 12 months preceding the period. Any program participant with no hospitalisation in the preceding 12 months will be excluded from propensity-based analyses.
- Step 3:** Within each stratum/period, calculate propensity score using a logistic regression modeling the probability of getting enrolled in the program. Covariates will include all variables considered for adjusted analyses.
- Step 4:** Within each stratum/period, starting with the earliest period, match 2 non-CDMP participants for each CDMP participant on the propensity score using optimal matching procedures. A control which has been used as a match in an earlier period is no longer available as match for a future period.
- Step 6:** Check the quality of the matching by plotting the propensity score distribution between the cases and controls overall and by period and by calculating the standardised difference for every covariate included in the propensity score calculation.

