#### *Analysis of matched data*

The matched set will be analysed using Poisson regression with generalized estimating equations to account for the matched-nature of the data. The outcome will be the event rate (e.g. rate of avoidable hospitalisations) occurring after the “matching-period”.

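### The primary matched analysis selects controls by their never enrolling later, does not require them to be alive when follow-up starts, and leaves that start undefined

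*SAP*

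**What the plan says.** SAP section 3.3.1 states that "The primary analysis for assessing the effect of the program will be performed using a propensity-matched cohort as the comparator".

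Under *Propensity scoring and matching*:
- Controls: "Matched controls will be selected from the APDC dataset using individuals who never got enrolled into the program".
- Step 1: "Group program participants by period (e.g. month/quarter/semester) according to their enrolment date". The length of the period is left open.
- Step 2: "For each stratum/period, obtain details of the latest hospitalisation occurring in the 12 months preceding the period". It continues: "Any program participant with no hospitalisation in the preceding 12 months will be excluded from propensity-based analyses". This exclusion is written for participants; controls are not mentioned.
- Step 4: "match 2 non-CDMP participants for each CDMP participant on the propensity score using optimal matching procedures".

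Under *Analysis of matched data*: "The outcome will be the event rate (e.g. rate of avoidable hospitalisations) occurring after the" matching-period. The SAP uses that term nowhere else and does not define it.

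Related text elsewhere:
- Section 3.2.1 treats death as censoring, but for the six-month rates of the programme cohort. Section 3.3 has no counterpart.
- Section 3.1 lists deaths as a secondary outcome.
- Section 1.1 covers enrolments from January 2011 to December 2013. Section 1.2 ends hospital data in December 2013.
- Section 1.4 supplies all deaths recorded in NSW from 2007 to 2013, not only those of participants.

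**The concern.** A matched cohort estimates a programme effect cleanly when eligibility, group assignment and the start of follow-up refer to the same moment in both groups. Three gaps stand in the way here.

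1. **Conditioning on the future.** Someone eligible as a control in early 2011 who enrols in 2013 is removed from the 2011 pool because of what happened later. People who die early cannot enrol later, so they are over-represented among the never-enrolled. If enrolment also follows hospital use, heavy users are removed from the pool.
2. **Unequal survival requirement.** A participant has survived to enrolment. A control's qualifying admission may have ended in death, or death may have followed before follow-up began.
3. **Start and end of follow-up.** With the matching-period undefined and no censoring rule, two analysts could build different person-time from the same data.

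At stake are the primary outcome, the rate of avoidable hospitalisations, and any matched comparison of deaths.

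**Working it through.** The SAP gives no mortality, uptake or event rate, so there is no planned figure to reproduce. All mortality and uptake values below are assumptions.

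**Reading A: follow-up starts at the end of the enrolment period.**

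Inputs: annual mortality m = 10%, 15% or 25%, the same in both groups; constant hazard h = −ln(1 − m) = 0.1054, 0.1625 or 0.2877; a control's latest admission uniform over the 12-month look-back; enrolment uniform within a period of L years.

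- Controls alive at the start of the period: A = (1 − e^(−h))/h = m/h = 0.949, 0.923, 0.869.
- Controls dead at the end of the period: 1 − A(1 − m)^L.
- Participants dead at the end of the period: 1 − [1 − (1 − m)^L]/(hL).

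| Dead at start of follow-up | m = 10% | m = 15% | m = 25% |
|---|---|---|---|
| Controls, month (L = 1/12) | 5.9% | 8.9% | 15.2% |
| Participants, month | 0.4% | 0.7% | 1.2% |
| Controls, semester (L = 0.5) | 10.0% | 14.9% | 24.7% |
| Participants, semester | 2.6% | 4.0% | 6.9% |

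These are shares of eligible controls before matching. They also assume that controls must have an admission in the look-back, which the SAP states only for participants.

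*If the dead are given full person-time*, a programme with no effect shows a rate ratio equal to the participants' share alive over the controls' share alive. For semester grouping this is 0.974/0.900 = 1.08, 0.960/0.851 = 1.13 and 0.931/0.753 = 1.24. For month grouping it is 0.996/0.941 = 1.06, 0.993/0.911 = 1.09 and 0.988/0.848 = 1.17.

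*If death is censored*, the dead add no person-time. With semester grouping the living controls per living participant are 2 × 0.900/0.974 = 1.85, 2 × 0.851/0.960 = 1.77 and 2 × 0.753/0.931 = 1.62, instead of 2.

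*Lost follow-up.* Uniform enrolment over 36 months gives a mean of 18 months after enrolment. Starting at the end of the period discards on average half a period: 0.5, 1.5 or 3 months for month, quarter or semester (0.5/18 = 2.8%, 1.5/18 = 8.3%, 3/18 = 16.7%). The last stratum, 1/36, 1/12 or 1/6 of the enrolment window, has no follow-up because data end in December 2013.

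**Reading B: the matching-period is the look-back, so follow-up starts at the beginning of the enrolment period.**

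Participants then carry time before enrolment that is unexposed and during which they cannot die. Take deaths over 12 months from the start of the period, semester grouping and m = 10%. A participant is at risk for about 0.75 year on average, so the null ratio is about (1 − 0.9^0.75)/0.10 = 0.076/0.10 = 0.76, even with all controls alive at the start. For m from 5% to 20% it is 0.75–0.77 (semester), 0.88–0.89 (quarter) and 0.96 (month).

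**The never-enrolled rule by itself.**

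A simulation of a programme with no effect was run for the first semester stratum under Reading A. It used gamma frailty with variance 1, 0.8 admissions a year, 12-month mortality of 5% or 15%, and groups standardised on prior admissions. Enrolment had probability 2%, 10% or 20% in each month with an admission. The reference is controls alive and not yet enrolled at the start, followed to death or the end of data.

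- Rates with death censored: the never-enrolled rule multiplies the rate ratio by 1.04, 1.21 or 1.49 as uptake rises (for example 1.331/1.282 = 1.04 and 1.990/1.340 = 1.49, both at 5% mortality).
- Rates without censoring: a factor of 1.10 to 2.06.
- Deaths, with never-enrolled controls alive at the start: a factor of 0.80 to 0.99. With dead controls kept in the denominator: 0.94 to 1.30.

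The link between admission and enrolment is an assumption. It also leaves a ratio of about 1.3 for rates in the reference itself, so only the factors relative to the reference are informative.

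**The case against.** The strongest defence is that these are gaps in wording. The SAP analyses event rates, section 3.2.1 shows how it handles death in rates, and the death register covers everyone. An analyst who carried that rule over would give dead controls no person-time. This stands for the rate: dead controls would then cost only precision. It does not cure the never-enrolled rule, and section 3.2.1 is written for the programme cohort.

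Several stronger readings are tempting but not supported.

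- *That the comparison has no common starting point, or that starting after the enrolment period is itself immortal-time bias.* A start at the end of the period is a shared calendar landmark. It is acceptable if both groups must be alive, and controls not yet enrolled, on that date. Its own cost is lost follow-up.
- *That participants are guaranteed alive when follow-up starts.* They are guaranteed alive only at enrolment; on Reading A some die before the landmark.
- *That the plan deliberately includes dead controls.* It omits a rule; it does not say this.
- *That an admission triggers enrolment, or that sicker people enrol later.* The SAP says neither.
- *That the bias has a known direction.* On the assumptions above, rates are pushed mostly against the programme, while deaths can move either way.

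Also fair: semester is the longest grouping offered, and month grouping gives smaller figures. The text on matched outcomes offers avoidable hospitalisations only as an example and does not name deaths.

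**Conclusion.** The point holds as a design weakness in the primary analysis. Control status depends on the future to December 2013, survival to the start of follow-up is required of neither group and is less assured for controls, and neither the start nor the censoring of follow-up is fixed.

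If follow-up starts at the end of the period and the dead keep person-time, the null rate ratio is about 1.06 to 1.24 for the mortality and grouping ranges shown. If death is censored, the rate bias comes from the never-enrolled rule: about 1.04 at low assumed uptake and 1.49 at high uptake. If follow-up starts at the beginning of the period, guaranteed survival favours the programme on deaths.

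None of these is an estimate for this study. Size and direction depend on the reading, the outcome, mortality and uptake, and the SAP gives none of the figures needed. Several defensible readings that give different answers are a reason to settle the rule before analysis.

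**What to change.** Rewrite the matching steps and the analysis paragraph of section 3.3.1 as follows.

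1. Define one start date per matched set: the participant's enrolment date, assigned also to the controls, or a common landmark at the end of the period. Drop or define the term matching-period.
2. Require the participant and both controls to be alive on that date, using the RBDM deaths.
3. Require controls to be not yet enrolled on that date, in place of never enrolled.
4. Apply the 12-month prior-admission rule to both groups.
5. Count events and person-time from that date to death, a control's own later enrolment, or 31 December 2013, whichever comes first.
6. If the landmark is chosen, state that the last stratum contributes nothing and that the effect applies to those who survive to the landmark.

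The cost is SAP wording and moderate programming; enrolment dates (section 1.1) and deaths (section 1.4) are already specified. There is a statistical cost too: censoring controls when they enrol may be informative if enrolment follows hospital use, so report a sensitivity analysis without that censoring. A person may also serve first as a control and later as a participant, and the variance estimate should allow for this.
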